### Primary outcome measures

#### Community Integration Questionnaire

The Community Integration Questionnaire (CIQ) is a 15-item questionnaire that assesses the level of participation in society [30]. The CIQ comprises three scales, namely home integration, productive activity, and social integration.

#### Impact on Participation and Autonomy

The Impact on Participation and Autonomy (IPA) is a 39-item questionnaire that focuses on two aspects of participation, namely perceived participation and the experience of problems [31].

#### EuroQol 6D

The EuroQol 6D (EQ-6D) is a generic quality of life measure consisting of 6 items (mobility, self-care, usual activities, pain/discomfort, anxiety/depression and cognition) each with three answer possibilities [32]. In addition, participants are asked to give a general rating of their current health state on a visual analogue scale, ranging from 0 to 100.

#### Medical Outcomes Study 36-item Short Form Health Survey

The Medical Outcomes Study 36-item Short Form Health Survey (SF-36/RAND 36-item Health Survey) is a 36-item generic quality of life questionnaire that measures several domains of perceived health [33].

#### Quality Of Life after Brain Injury

The Quality Of Life after Brain Injury questionnaire (QOLIBRI) is a brain injury specific quality of life measure. The QOLIBRI consists of 49 questions that measure health related quality of life within six domains (physical condition, thinking activities, feelings and emotions, functioning in daily life, relationships and social/leisure activities, current situation and future prospects) [34].

### Secondary outcome measures

#### Cognitive Failures Questionnaire

The Cognitive Failures Questionnaire (CFQ) is a 25-item questionnaire on self-reported cognitive failures [35]. Both the patient as well as his or her caregiver will be asked to fill out this questionnaire to evaluate the cognitive status of the patient.

#### Cognitive Log

The Cognitive Log (Cog-log) is a 10-item cognitive screening instrument [36]. It measures higher neurocognitive processes including orientation, memory, concentration and executive skills.

#### Adult Memory and Information Processing Battery Task A

The Adult Memory and Information Processing Battery (AMIPB) Task A is a measure for information processing speed [37]. In this test, the subject is asked to select the second highest number in each row of five. The final score is the number of correct choices made in two minutes.

#### Paragraph Recall

The Paragraph Recall (PR) is a test for immediate and delayed verbal memory [38]. The subject is asked to recall as much as possible from a paragraph, which is read to the subject aloud. This will be performed both directly, and, without warning, again 20 minutes later. To prevent interference with the paragraph from the previous measurement, a different paragraph will be used each time.

#### Trail Making Test

The Trail Making Test (TMT) measures scanning, visuomotor tracking, divided attention and cognitive flexibility [39]. The test is divided into two parts, part A and B. In part A, the subject is asked to connect consecutively numbered circles on one work sheet as fast as possible. In part B, the subject is asked to connect consequently numbered and lettered circles. The time needed to complete part A and part B is recorded.

#### Verbal Fluency Test

During the Verbal Fluency Test (VFT), the subject is asked to name as many words from one semantic category, in this case animals, in one minute [40].

#### Hospital Anxiety and Depression Scale

The Hospital Anxiety and Depression Scale (HADS) is a commonly used questionnaire, which was designed to detect the presence of mild degrees of mood disorders in non-psychiatric hospital outpatients [41]. The HADS consists of 14 items, and has two sub-scales, namely depression and anxiety.

#### Impact of Event Scale

The Impact of Event Scale (IES) measures psychological reactions that can take place after a traumatic event. The IES has 15 items and explores the level of posttraumatic stress by asking for intrusive and avoidance symptoms [42,43].

#### New York Heart Association Classification

The New York Heart Association Classification (NYHA-classification) is a functional classification system that divides cardiac patients into four classes depending on their limitation in physical activities [44].

#### Fatigue Severity Scale

The Fatigue Severity Scale (FSS) is a 9-item questionnaire that measures experienced severity of fatigue symptoms in daily activities [45].

#### Barthel Index

The Barthel Index (BI) is a widely used instrument that measures basic (personal) activities of daily living (ADL). The instrument consists of 10 items and measures to what extent a person can perform basic ADL activities independently [46].

#### Frenchay Activities Index

The Frenchay Activities Index (FAI) is an accepted measure for instrumental ADL that reports on fifteen daily life activities [47]. Compared to the Barthel Index, the measured activities are of a higher level, for example the preparation of meals, doing groceries, making trips and performing paid labour.

#### Caregiver Strain Index

The Caregiver Strain Index (CSI) is a 13-item, dichotomous scale that has to be filled out by a partner, caregiver or significant other [48]. The CSI measures strain related to the provision of care.

### Parameters for process evaluation

The intervention will be evaluated based on information from the specialised nurses and the participants. First, the intervention process will be evaluated based on information provided by the specialised nurse. He/she will record the following items: the actual number of consultations (face-to-face, by telephone and by email), the direct time related to each consultation, the indirect time related to each consultation (administration, travel time), the provision of information per consultation, the use of the screening tools, the kind of problems presented, number of referrals, completion of the intervention according to protocol and, in case of non-compliance, reason for non-compliance. Second, after completion of the intervention the participant and his/her caregiver will be asked to fill out a questionnaire to evaluate the intervention.

### Determination of costs

Data concerning costs will be gathered prospectively using monthly cost-diaries [49]. All the participants receive cost-diaries in which they are asked to note all their health care utilisation during that month. To prevent non-compliance, the research assistant will give a phone call at the end of each month and will record the health care utilisation of that month. For the calculation of the total costs, three categories can be distinguished, namely direct health care costs, direct non-health care costs and indirect costs. For the determination of the direct health care costs the following variables will be recorded: duration admission in health care facility, visits physicians and other health care providers and amount of prescribed medication. Direct non-health care costs that will be measured, are the costs of informal health care, over-the-counter medication, costs of health activities, hours of paid or unpaid household help and special aids. The indirect costs comprise loss of paid and unpaid work productivity of the patient.

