### Group allocation and intervention

The intervention group will receive an early intervention service delivered by a specialised nurse in addition to usual health care available to all patients, whereas the control group will only receive usual health care. The intervention period will extend up to three months after the cardiac arrest. During this period a specialised nurse will provide one to six consultations for the patient together with his or her caregiver (if present). The number of consultations will be tailored for each individual participant and will depend on the severity of the problems and the needs and wished of the patient and their caregiver. The consultations will take place in the hospital or at the participants' home. In between the consultations the participants have the opportunity to contact the nurses by phone or email. During the intervention period the specialised nurse will screen for cognitive and emotional problems. Next to that, information will be provided by means of an information booklet and by discussing questions that the participants may have. Furthermore, emotional and practical support will be offered and self-management will be explained and promoted. A consultant in rehabilitation medicine supervises the specialised nurses. If necessary, referral to additional diagnostics or specialised rehabilitation care can take place.

There will be no restrictions on possible co-interventions. Participants assigned to the intervention group who do not want treatment will still be approached for all the follow-up measurements.

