### Data collection

Baseline measurements will be administered two weeks (= T1) after the cardiac arrest, with further assessments at three (= T2) and twelve months (= T3). The measurements will be administered wherever the patient is at that time. A research assistant, who will be blinded to the group allocation, will perform the assessments.

To check for the effectiveness of blinding, the research assistants will be asked after the last measurement to indicate whether they think the participant belonged to the intervention group or the control group.

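### The monthly calls on health care use go to the same role that must assess outcomes blind, and can reveal allocation before T2 and T3

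*Protocol article*

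**What the plan says.** On assessment, the Data collection section states: "A research assistant, who will be blinded to the group allocation, will perform the assessments". It adds one check on blinding: "the research assistants will be asked after the last measurement to indicate whether they think the participant belonged to the intervention group", or to the control group.

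On costs, the Determination of costs section states: "All the participants receive cost-diaries in which they are asked to note all their health care utilisation during that month". To keep compliance up, "the research assistant will give a phone call at the end of each month and will record the health care utilisation of that month". The direct health care items include "visits physicians and other health care providers and amount of prescribed medication".

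On the difference between arms, Group allocation and intervention gives the intervention group one to six consultations with a specialised nurse within the first three months, plus access to the nurse by phone or email, "whereas the control group will only receive usual health care".

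Parameters for process evaluation separately has the nurse record the number of consultations (in person, by telephone and by email) and the direct and indirect time spent on each.

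**The concern.** The role described as blinded is also given a task that asks about the one kind of care that differs by design between the arms. A patient who answers the monthly call fully will mention the nurse. This is more than the usual risk of a chance remark, because the data collection procedure itself asks for the information, repeatedly, and before both post-randomisation assessments.

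At stake is detection bias. An assistant who knows the allocation may encourage, prompt or score differently. Assessor blinding is the only blinding the article describes, so if it fails through procedure, the trial report could not safely repeat the claim. Scores already collected could not be corrected afterwards. The single allocation guess comes after the last measurement. It can reveal unblinding but cannot prevent it, and by then a correct guess may reflect either disclosure or the outcome the assistant has observed.

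**Working it through.** The article gives no figure on this point to reproduce. The check compares sections and adds a simple timeline.

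**1. Is it the same role?** Data collection and Determination of costs both use the title research assistant. No other caller is named, and no caller is described as unblinded.

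**2. Does the call elicit allocation?**
- The diary covers all health care use, and the call records that month's use. Providers other than physicians are listed. Trial-nurse contacts are not excluded.
- Specialised-nurse consultations belong to the intervention arm only.
- The Background says that no specific follow-up programmes or nursing interventions for cardiac arrest survivors exist in the Netherlands. A reported specialised-nurse visit is therefore a strong, though not perfect, marker of allocation.

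**3. When do the calls fall?** Inputs: T1 at two weeks (about 0.5 month), T2 at 3 months and T3 at 12 months (Data collection); randomisation after T1 (Recruitment and randomisation); intervention up to 3 months (Group allocation and intervention). Assumption: calls are made monthly from T1 to T3, since the article gives no start or end date for them.
- T1 to T2: 3 − 0.5 = 2.5 months, so about 2 to 3 calls, all within the intervention period.
- T2 to T3: 12 − 3 = 9 months, so about 9 calls.
- T1 to T3: 12 − 0.5 = 11.5 months, so about 11 to 12 calls.

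Disclosure is most likely in the first 2 to 3 calls, and what is learned there carries over to T3. T1 precedes randomisation and is unaffected.

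**4. Which outcomes are exposed?**
- *Most exposed:* the secondary cognitive tests given in person, namely Cog-log, AMIPB Task A, Paragraph Recall, Trail Making and Verbal Fluency.
- *Less exposed:* the primary measures (CIQ, IPA, EQ-6D, SF-36, QOLIBRI). These are questionnaires, and the patients answering them know whether they saw a nurse.
- *Unclear:* NYHA class, because the article does not say who rates it.

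**5. How large is the bias?** The article gives neither the proportion of patients who would disclose nor the effect of disclosure on scores. No estimate can be derived from it.

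**The case against.** **The same person may not do both tasks.** Data collection also speaks of assistants in the plural, and dividing tasks among staff is a detail that a condensed article may leave to the full protocol. A reader might infer that each assessor phones his or her own patients, so that the claim of blinded assessment is false. The text does not say that. What stands is narrower: two stated procedures conflict as written, and no stated safeguard separates them.

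**Not every intervention patient would be identified.** A reader might infer that nearly all would be, since each treated patient has at least one consultation. The article does not support this. It foresees patients allocated to the intervention who do not want it, it leaves co-interventions unrestricted in both arms, and recall may be poor in patients with cognitive impairment. Many could be identified; how many is unknown.

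**The primary comparison is not mainly at risk.** A reader might extend the worry to the primary questionnaires through help with completing them. The article describes no such help, and assessor blinding cannot remove reporting bias in patients who know their care. This objection largely stands. The assistant performs the assessments with no stated exception for questionnaires, so some exposure remains, but it is secondary.

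**Several cognitive tests are scored by count or time.** AMIPB, Trail Making and Verbal Fluency leave the rater little discretion. That limits scoring bias but not the effect of encouragement or prompting.

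**The end-of-study guess is a recognised check.** That is fair, and the article presents it as a check, not a safeguard. A further guess at T2 would be optional, and it could itself prompt assistants to think about allocation before T3.

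**Conclusion.** The point holds as a conflict between two sections. As written, the blinded role makes about 2 to 3 calls before T2 and about 9 more before T3 that can reveal the allocation of many intervention patients. This assumes monthly calls from T1 and no unstated separation of caller from assessor. If the full protocol already separates them, one sentence in the text settles the matter.

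The risk of detection bias falls mainly on the secondary cognitive tests at T2 and T3. It is smaller for the primary outcomes, and its size cannot be stated. The issue should be fixed because the repair is cheap and unblinded scores cannot be put right later, but it is not a demonstrated failure of the primary comparison.

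**What to change.** Reconcile Data collection with Determination of costs by stating two rules:

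1. No research assistant makes the cost calls to, or handles the cost diaries of, a patient whom he or she assesses.
2. Contacts with the trial nurse are left out of the diary and the call, with the same instruction in both arms, and are taken for the economic evaluation from the nurse's own log described under Parameters for process evaluation.

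The first rule matters more. Referrals made by the nurse would still appear in the calls and could hint at allocation even with nurse contacts left out. The second rule loses little, since the nurse already records the number, mode and time of consultations.

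The cost is some rescheduling among existing assistants, whose number per site is not stated. Where a site has only one assistant, the fallback is the second rule plus asking participants not to mention the nurse; this protects less well. Cutting the calls down to reminders is less attractive, because they exist to secure compliance and cost data could be lost.

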### Statistical analysis

#### Effect evaluation

Descriptive techniques will be used to present data concerning the participants, number of dropouts, losses-to-follow up and the scores on the outcome measures.

To determine whether the patients participating in this trial are representative for the population of cardiac arrest survivors, the baseline characteristics between compliant and non-compliant participants, as well as dropouts and losses-to-follow up will be compared.

Before examining the effectiveness of the intervention, the comparability of the two groups will be checked. Baseline characteristics will be compared using independent sample T-test (normal distribution) or Mann Whitney U-test (non-normal distribution), in case of a continuous variable. In case of a dichotomous variable a chi-square test will be used.

The data from the evaluation study will be analysed according to the intention-to-treatment principle. If either T1 or T2 data are missing the 'last-observation-carried-forward' principle will be used.

Multiple regression analysis, adjusted for possible differences in baseline characteristics or baseline scores, will be applied to examine differences between the intervention and the control group on the primary outcome measures at T3 (one year after the cardiac arrest). If there is a difference between the groups, the effect size will be calculated. Subgroup analysis will be performed for potential effect modifiers.

To assess whether protocol deviations or care provided outside the intervention have caused biases, the results of the intention-to-treatment analysis will be compared to the on-treatment analysis.

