## Methods/Design

### Study design

The study presented in this paper is a randomised, controlled clinical trial in which the effect of an early intervention service will be investigated. Participants will be followed over one year. During this year, three measurements will take place, namely two weeks, three months and twelve months after the cardiac arrest (see flow diagram, Figure 1). The Medical Ethics Committee of University Hospital Maastricht/Maastricht University approved the study protocol. The study is registered in a public trial registry [ISRCTN74835019]. This study is part of a larger research project, which also comprises a prospective and prognostic cohort study.

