### Recruitment and randomisation

Between three and ten days after the cardiac arrest the patient and caregiver will be approached to participate in the study by their treating physician. Standard procedures concerning informed consent will be used. Both patients and caregivers sign an informed consent form if they decide to participate in the study. In case the patient is still unconscious or incapacitated at the moment that informed consent is needed, the caregiver will be asked to give provisional informed consent. When the patient regains consciousness, definitive informed consent will be sought.

Participants will be randomly allocated to either the intervention group or the control group. The randomisation will take place after the baseline measurements (2 weeks after the cardiac arrest) and will be performed centrally by the project leader using a computerised block randomisation. The randomisation scheme includes prestratification on two variables, namely hospital site and location of the cardiac arrest (in-hospital versus out-of hospital). Two series of opaque numbered envelopes will be prepared for each hospital site (one for in-hospital and one for out-of-hospital cardiac arrests), filled with a card indicating the allocated group. After registration, the envelope will be opened and the specialised nurse will be informed about the patients that are allocated to the intervention group.

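### Two secondary checks cannot answer the questions set for them: representativeness is judged among enrolled patients only, and bias is judged from the gap between intention-to-treat and on-treatment results

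*Protocol article*

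**What the plan says.** Both checks are in the protocol article, Statistical analysis, Effect evaluation.

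- **Check 1.** Its purpose is given as "To determine whether the patients participating in this trial are representative for the population of cardiac arrest survivors". Its method is that "the baseline characteristics between compliant and non-compliant participants, as well as dropouts and losses-to-follow up will be compared".
- **Check 2.** Its purpose is given as "To assess whether protocol deviations or care provided outside the intervention have caused biases". Its method is that "the results of the intention-to-treatment analysis will be compared to the on-treatment analysis".

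Other sections bear on these checks:

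- Recruitment and randomisation describes selection before enrolment. The treating physician approaches patients between days 3 and 10, and consent is needed: "Both patients and caregivers sign an informed consent form if they decide to participate in the study".
- Study design mentions a possible outside reference group: "This study is part of a larger research project, which also comprises a prospective and prognostic cohort study". The Effect evaluation section does not use it.
- Group allocation and intervention says that intervention patients who do not want the service are still followed up, and that referral to further care is part of the service. On other care it says: "There will be no restrictions on possible co-interventions".

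**The concern.** Each check states a purpose and then names a comparison that cannot serve it.

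Check 1 asks whether the people inside the trial resemble survivors in general, but every group compared is inside the trial. A reassuring result could be reported as representativeness when it shows only that those who stayed resemble those who left. The Discussion aims the results at a decision on introducing the service in Dutch health care, so the difference matters for how the findings are applied.

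Check 2 treats the relation between two estimates as a test for bias. One estimate keeps the randomised groups and the other does not. A gap could therefore cast doubt on a sound ITT result, and agreement could be read as more reassurance than it gives. The comparison also cannot isolate outside care, which is unrestricted in both arms.

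**Working it through.** **Check 1: no arithmetic applies.** Consider three groups: (a) survivors who meet Table 1 but decline or are never approached, (b) enrolled patients who comply and stay, (c) enrolled patients who do not comply or are lost. Representativeness concerns (b) and (c) together against (a). The planned comparison is (b) against (c), and (a) appears nowhere in it. So (b) and (c) can look identical while both differ from (a), or differ while the enrolled group as a whole resembles (a). Reading non-compliant as consent refusers does not rescue the check. The sentence says participants, and Parameters for process evaluation uses non-compliance for not completing the intervention.

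**Check 2: inputs.**

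- From Study population: CIQ mean 16.09, SD 4.20, relevant difference 10%, one-sided alpha 0.05, power 0.8, 84 per group, 15% loss, 200 in total.
- Assumed, not in the documents: true effect zero; a share c of the intervention arm declines, c = 5% to 30%; decliners score g SD below the others, g = 0.25 to 0.5; the control arm contains the same mix but nobody there is removed.

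**The plan's own figures first.** Target difference: 0.10 × 16.09 = 1.609. Per group: 2 × [4.20 × (1.645 + 0.842) / 1.609]² = 84.25, against 84 stated. With loss: 168 / 0.85 = 197.6, so 198, against 200 stated. Both agree closely enough, and the point does not depend on them.

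**Spurious on-treatment difference when ITT is truly zero.** Set the mean of those who accept at 0.

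- The whole control arm then averages −c × g × SD.
- If decliners are dropped, the difference is c × g × SD.
- If decliners are moved to the control group, that group averages −2c × g × SD / (1 + c), and the difference is 2c × g × SD / (1 + c).

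| c | g | Dropped: points (% of 1.609) | Moved: points (% of 1.609) |
|---|---|---|---|
| 5% | 0.25 | 0.05 (3%) | 0.10 (6%) |
| 5% | 0.5 | 0.11 (7%) | 0.20 (12%) |
| 10% | 0.5 | 0.21 (13%) | 0.38 (24%) |
| 20% | 0.5 | 0.42 (26%) | 0.70 (44%) |
| 30% | 0.5 | 0.63 (39%) | 0.97 (60%) |

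For example, 0.30 × 0.5 × 4.20 = 0.63, and 0.63 / 1.609 = 39%. If decliners do better than the rest, the sign reverses. These values are before baseline adjustment.

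**The converse.** A real bias in one direction and selection in the other can cancel, so agreement between the two results does not show absence of bias.

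**Outside care.** An on-treatment set defined by taking up the service leaves unrestricted care in both arms as it was. Because referral is part of the service, a difference in later care between arms can be an effect of the service.

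**The case against.** The strongest reply is that these are modest, conventional checks.

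- **ITT stays the analysis.** No rule lets the on-treatment result override it, and a supportive on-treatment analysis is common and not an error. This stands. A reader might infer that the plan would replace ITT, but the text says only that the two will be compared. The fault is the inference about bias drawn from that comparison.
- **Tailoring is adherence.** The number of consultations "will depend on the severity of the problems and the needs and wished of the patient and their caregiver". A reader might infer that on-treatment status therefore depends on severity. It does not follow: one visit for a mild case is treatment as planned, and the article does not define the on-treatment set. The point rests on patients being free to decline, and a link between declining and prognosis is possible but not shown.
- **The gap may be small.** With 84 per group the standard error of a difference is about 4.20 × √(2/84) = 0.65, so even 0.63 lies within one standard error. The planned regression also adjusts for baseline differences, which may shrink the gap. This stands as a limit on size. Adjustment reaches only what was measured.
- **Vulnerable groups are not shut out.** A reader might infer that unconscious patients or those without a caregiver are missing. The documents do not support that. Recruitment and randomisation allows provisional consent by the caregiver, and consultations include the caregiver only if there is one. Decliners and survivors not approached are enough for the point.
- **Reference data may exist.** The parent cohort could supply them, and a condensed article need not describe a screening log. That is fair: the finding is that the stated comparison does not match the stated purpose, not that a log is missing.

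**Conclusion.** The point holds for both checks, as a matter of secondary analyses and their interpretation. Check 1 can describe adherence and attrition but cannot support a statement about representativeness. Check 2 cannot tell bias from selection: the on-treatment result can differ from an unbiased ITT result, though it need not, and agreement proves little. It also does not isolate outside care.

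For check 2 the size is illustrative only: 0.05–0.63 CIQ points if decliners are dropped, or 0.10–0.97 (6–60% of the target) if they are moved to control. This assumes no true effect, 5–30% declining and a 0.25–0.5 SD deficit, none of which the documents give. For check 1 the article offers no figure from which to size the error. The primary ITT comparison and the sample size are untouched.

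**What to change.** **Check 1.** Call the planned comparison an adherence and attrition check. Assess representativeness by comparing randomised patients with eligible survivors who were not randomised, on basic items (age, sex, hospital, in-hospital or out-of-hospital arrest), using screening counts or the parent cohort where available. If neither is available, drop the representativeness conclusion.

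**Check 2.**

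- State that the effect conclusion rests on ITT alone and that a gap from the on-treatment result will not be read as evidence of bias. Any on-treatment result is supportive only.
- Estimate the effect of receiving the service as a complier-average causal effect, with receipt defined as at least one nurse consultation, taken from the records in Parameters for process evaluation. Controls receive usual care only, so without covariates this is the ITT difference divided by the proportion who received the service. It is zero whenever the ITT difference is zero. State the exclusion restriction: allocation affects outcome only through receiving the service.
- The complier-average estimate does not deal with outside care. For that, tabulate care use by arm from the monthly cost diaries (Determination of costs), and report differences as a result, not as bias.

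**Cost.** A little extra analysis, modest screening data, and a wider interval for the complier effect. Treating the proportion as fixed, the width grows by 1 / (1 − c): 1 / 0.95 = 1.05 times at 5% declining and 1 / 0.70 = 1.43 times at 30%. The consultation and care-use data are already planned.
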